### Outcome measures

#### Psychological distress

Psychological distress over the past 30 days will be measured using the Kessler 10-item psychological distress scale (K-10 [36];). The K10 is a self-report measure comprising 10 items on a 5-point scale. Total scores range from 10 to 50; scores above 15 indicate moderate to severe psychological distress, while scores greater than 20 indicate higher likelihood of mental disorder [1].

#### Self-compassion

Self-compassion will be measured using the Short Form of the Self-Compassion Scale (SCS-SF [50];). This self-report scale consists of 12 items designed to measure the six subcomponents of self-compassion: mindfulness, overidentification, common humanity, isolation, self-kindness (e.g. “I try to be understanding and patient towards those aspects of my personality I don’t like”) and self-judgement; each item is rated on a 5-point scale. Item scores are used to generate a total self-compassion score, which has a high correlation with the total score of the long form Self-Compassion Scale [50]. Psychometric studies have demonstrated the reliability and validity of both forms of the Self-Compassion Scale with adolescents and young adults.

#### Emotion regulation difficulties

Emotion regulation difficulties will be measured using the Difficulties in Emotion Regulation Short Form (DERS-SF), a widely-used 18-item measure of emotion regulation problems [35]. This self-report scale measures difficulties with emotion regulation along six dimensions: (1) awareness of emotions; (2) emotional clarity; (3) acceptance of emotions; (4) access to emotion regulation strategies; (5) ability to engage in goal-directed behaviour when experiencing negative emotions; and (6) impulse control in the face of difficult emotions. The DERS-SF provides a total scale score for emotion regulation difficulties and is a valid and reliable measure of difficulties with emotion regulation in both adolescents and adults [35].

#### Coping

Coping will be measured using the brief COPE [11], a 28-item self-report measure of coping strategies which is a short version of the original COPE scale. Respondents rate items (e.g. “I take action to try to make the situation better”) across 14 subscales, using a 4-point scale. The subscales can be categorised into those representing approach coping (active coping, emotional support, use of informational support, positive reframing, planning, and acceptance) and those representing maladaptive coping (denial, self-distraction, substance use, venting, self-blame, and behavioural disengagement) subscales. Avoidant coping has been associated with poor physical health outcomes in adults with chronic medical conditions [18]. The Brief COPE has good internal reliability [11] including among adolescent samples [30].

#### Wellbeing

Wellbeing will be measured using the World Health Organization Wellbeing Index (WHO-5), a widely-used, validated measure of subjective wellbeing designed for use in clinical trials [62]. The WHO-5 measures positive psychological well-across 5-items using a 6-point scale, and scores are used to obtain a percentage score ranging from 0 to 100. The WHO-5 displays acceptable psychometric properties among adolescents [7] and adults [6].

#### Quality of life

The Assessment of Quality of Life – 6 Dimension (AQoL-6D) is a generic, multi-attribute utility, preference-based measure that will be used to assess health-related quality of life [44]. It is an adaptation of the adult AQOL-6D utility instrument and has 20 items across six dimensions - independent living, mental health, coping, relationships, pain, and senses. There are scoring algorithms for both Australian adults and adolescents for the AQoL-6D [44].

#### Health resource use

A health resource use questionnaire was developed for the purposes of the study, based on the core items for a standardized resource use measure highlighted by Thorn et al. [61]. This measure asks about frequency of health service use, frequency and length of stay for hospital admissions, and frequency and dose of medication use over the past month. It will be used to collect resource use data for the purposes of the cost-utility analysis (CUA).

#### Program engagement and adherence

Program engagement will be measured using online program metrics, including log-ins, time spent in program, and module completion, as well as self-report of engagement with practice outside of program. These variables will be treated as a measure of program feasibility and will also be explored as potential moderators of treatment effects. Program referrals and attrition data will also be gathered as a measure of program feasibility.

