**Fig. 1 Fig1:**
[figure not shown]
An overview of the Study Design

Following completion of the pre-test, participants will be randomised to conditions using the Qualtrics randomiser function. Participants in both arms of the trial will be contacted by a research assistant shortly after completing the baseline survey, who will inform them of their condition allocation, reiterate study procedures and answer any questions: as participants are recruited on a rolling basis, those assigned to SCO-CMC will receive access to the program as soon as the research assistant has made contact with them. At four and 12 weeks after completing baseline measures, all participants will be sent an email asking them to complete the outcome measure battery again. Following completion of the third set of measures, participants in the WLC will be contacted by the research assistant, who will provide a code for program access. All participants will receive up to two reminders to complete the measure battery at each time point; participants enrolled in the intervention will also receive an email or text reminder 2 weeks post enrolment to encourage them to continue progressing through the program.

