### Statistical analysis

#### Tests of intervention effects

We will perform Intention to Treat and Per Protocol analyses, conduct a sensitivity analysis [39], and compare complete cases versus cases lost to follow-up on baseline characteristics and scores on clinical measures, by randomisation group [64]. GLMM Mixed Model Repeated Measures will compare change in outcome measures across conditions, and time points, while controlling for random effects including age and gender. The group*time interaction will be calculated as a test of intervention effects. Using DASS-21 scores participants will be classified into outcome categories (Recovered, Improved, Unchanged, Deteriorated) according to Reliable Change Index and Clinical Significance of change at post-treatment and follow-up [32], to determine whether the SCO-CMC and control groups differ in clinically significant treatment outcome over time (Cochrane’s Q).

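### Program-use measures are named as moderators of the treatment effect, but up to week 12 they exist only in the SCO-CMC arm, so only an unrandomised within-arm association can be estimated

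*Protocol article*

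**What the plan says.** Under Program engagement and adherence, the protocol article defines the measures: "Program engagement will be measured using online program metrics, including log-ins, time spent in program, and module completion", together with self-reported practice outside the program. It gives them two roles: "These variables will be treated as a measure of program feasibility and will also be explored as potential moderators of treatment effects".

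The timing is under Recruitment, randomisation and allocation. Allocation follows the pre-test: "Following completion of the pre-test, participants will be randomised to conditions using the Qualtrics randomiser function". Access in the intervention arm comes later still: "those assigned to SCO-CMC will receive access to the program as soon as the research assistant has made contact with them". Outcomes are collected again at two points: "At four and 12 weeks after completing baseline measures, all participants will be sent an email asking them to complete the outcome measure battery again". The waitlist arm gets the program only after the second of these: "participants in the WLC will be contacted by the research assistant, who will provide a code for program access".

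Under Tests of intervention effects, the efficacy test is separate from engagement: "The group*time interaction will be calculated as a test of intervention effects". The same section names intention-to-treat, per-protocol and sensitivity analyses. The article names no method for a variable that arises after randomisation.

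**The concern.** A moderator of a treatment effect answers the question of whether the difference between arms changes with the level of some variable. For that, the variable must be defined in both arms and must not be a product of allocation. Program use meets neither condition over the period in which the arms are compared.

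What is left is a comparison of heavier with lighter users inside one arm. Participants who are less unwell, or already improving, may find it easier to log in and finish modules. The article itself describes pain and fatigue as challenges to keeping up treatment regimens (Intervention approach and theoretical basis). A pattern of more use and more improvement can therefore appear when the program does nothing. Under the label of moderation, a reader could take it for a finding with the authority of the randomised comparison.

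**Working it through.** The article gives no figure for this analysis, so there is none to reproduce.

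**Step 1: when and where the measures exist.**

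| Event | SCO-CMC | Waitlist |
|---|---|---|
| Pre-test, then randomisation | no program use yet | no program use yet |
| Baseline to week 12 | use accrues once access is given | no access, so no use |
| After the third set of measures | no further trial outcome | access given, no further trial outcome |

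Later waitlist use cannot help, because it follows that arm's last outcome.

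**Step 2: can a treatment-by-use interaction be estimated?** Let G = 1 for SCO-CMC and 0 for waitlist, and let U be use. The ordinary model is

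E(Y) = b0 + b1·G + b2·U + b3·G·U.

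With U = 0 whenever G = 0, the product G·U equals U for every participant, so

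E(Y) = b0 + b1·G + (b2 + b3)·U.

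Only the sum b2 + b3 can be estimated. A numerical check with 40 per arm gives a design matrix of rank 3 for 4 columns. The same holds at each visit of a repeated-measures model, where group-by-time-by-use coincides with time-by-use. If waitlist use is coded as missing instead, the control arm drops out. Either way, the quantity estimated is the slope on use within SCO-CMC.

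**Step 3: how easily that slope misleads.** Inputs from Sample size: a target of 48 per group, and 40 per group as the number required. Assumptions: the program effect is zero; use and spontaneous improvement are jointly normal with correlation r; the slope is tested two-sided at 5%. The documents give no r, so a range is shown.

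The slope is significant when the sample correlation exceeds c = t/√(n − 2 + t²).
- n = 48: t = 2.013, c = 2.013/√(46 + 4.052) = 0.2845
- n = 40: t = 2.024, c = 2.024/√(38 + 4.098) = 0.3120

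By Fisher's z, the chance of exceeding c is 1 − Φ{[atanh(c) − atanh(r) − r/(2(n − 1))]·√(n − 3)}. For n = 48 and r = 0.3 this is 1 − Φ[(0.2926 − 0.3095 − 0.0032) × 6.708] = 1 − Φ(−0.135) = 0.55.

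| Assumed r | n = 40, formula | n = 40, simulation | n = 48, formula | n = 48, simulation |
|---|---|---|---|---|
| 0 | 2.5% | 2.4% | 2.5% | 2.4% |
| 0.2 | 24% | 24% | 28% | 28% |
| 0.3 | 48% | 48% | 55% | 56% |
| 0.4 | 74% | 74% | 82% | 82% |

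Entries are the share of trials with a significant slope in the direction of benefit; the simulation used 20,000 trials per setting.

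**Step 4: apparent size at r = 0.3.** Split SCO-CMC at the median of use. The mean of the upper half of a standard normal is √(2/π) = 0.798, so high users improve about 0.3 × 0.798 = 0.24 SD more than waitlist and 2 × 0.24 = 0.48 SD more than low users. Simulation gives 0.23 to 0.24 and 0.47. The true program effect is zero throughout.

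**The case against.** The strongest reply is that the article gives no model. It does not write a group-by-use term, say how waitlist use is coded, or say which participants enter the analysis; a full analysis plan could specify a within-arm association or a complier-type estimate. The rank result therefore describes the ordinary reading of a moderator analysis, not a model the article prints. That stands, but it does not remove the point. The article has already assigned these variables the role of moderators of treatment effects, and a later plan would have to change that role, not fill in a detail.

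The percentages are also open to challenge: they are the power to detect a correlation that was put in. That is correct. They are not an error rate of this trial, and at r = 0 there is no inflation. They show only that a modest link between use and improvement is enough. Step 2 does not depend on them.

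One smaller reservation stands. For outside practice, the article does not say which arm is asked, so zero waitlist use on that item is inferred from the plain reading that it means practice of the program.

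Three stronger readings are tempting, and the documents do not support them.
- A reader might infer that the engagement analysis will be used to support efficacy or to state how much use is needed. The article says neither. Its test of intervention effects is group by time, and no hypothesis under Aims and hypotheses concerns engagement.
- A reader might infer that the main comparison is compromised. It is not; use does not enter that test as described.
- A reader might infer that the trial ought to test baseline moderators. Their absence is not an error, and with 40 to 48 per arm and many diagnoses, three-way interactions would be weak.

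**Conclusion.** The point holds as a fault in a stated analysis role. The use measures follow randomisation and, up to week 12, arise only in SCO-CMC, so an ordinary treatment-by-use interaction cannot be estimated. The estimable quantity is a confounded within-arm association. The non-identification rests on the access schedule in the article and on waitlist use being zero in that period; the illustrated frequencies rest in addition on the assumed r.

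Severity is minor. The article calls the trial exploratory and says these measures will be explored. The intention-to-treat analysis, the sample size and the data collection are untouched. It is still worth correcting, because the wording would mislead if followed.

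**What to change.** Under Program engagement and adherence:

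1. Keep the feasibility role and remove the statement that the engagement variables will be explored as moderators of treatment effects.
2. State instead that relations between engagement and outcome will be reported as descriptive associations within SCO-CMC, adjusted for the baseline score, and will not be read as effect moderation or dose-response.
3. State that any moderator analysis that is run will use only variables measured at pre-test in both arms. This is a limit on such analyses, not a request to add them.
4. Optionally, if an effect of use is wanted, estimate it with randomised arm as the instrument. With waitlist use at zero and no covariates, this is the difference between arms divided by mean use in SCO-CMC. It rescales the intention-to-treat effect and does not show whether heavier users benefit more. The plan must state the assumption that allocation acts only through use. That is open to doubt here, because participants are told their allocation and the intervention arm receives an additional reminder.

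Items 1 to 3 are wording changes that need no new data and no change to the sample size. Item 4, if taken up, adds an assumption to defend and gives wider intervals than the within-arm slope.

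### Programme engagement cannot be explored as a moderator of the treatment effect, because during the compared period it arises after randomisation and only in the SCO-CMC arm

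*Protocol article*

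**What the plan says.** Three parts of the protocol article bear on this.

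- **Outcome measures, Program engagement and adherence.** "Program engagement will be measured using online program metrics, including log-ins, time spent in program, and module completion". Participants are also to report how much they practise away from the platform. These variables serve first as feasibility measures. They "will also be explored as potential moderators of treatment effects".
- **Procedure, Recruitment, randomisation and allocation.** "Following completion of the pre-test, participants will be randomised to conditions using the Qualtrics randomiser function". After that, "those assigned to SCO-CMC will receive access to the program as soon as the research assistant has made contact with them". Outcomes are collected from everyone on the same clock: "At four and 12 weeks after completing baseline measures, all participants will be sent an email". The waitlist gets its access code last: "Following completion of the third set of measures, participants in the WLC will be contacted by the research assistant".
- **Statistical analysis, Tests of intervention effects.** The treatment effect is the group-by-time interaction in a mixed model, which is a contrast between the randomised arms.

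**The concern.** A moderator of a treatment effect tells us for whom the difference between arms is larger or smaller. That requires the moderator to have a meaning and a value in both arms and, for a causal reading, not to be a consequence of allocation. Programme engagement meets neither condition here. It begins after allocation, and the waitlist cannot produce it until after its final outcome.

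What is at stake is what the trial can say about engagement. The programme is self-guided, so participants choose how much of it to use, and the same motivation or state of health may drive both use and recovery. A finding that heavier users improved more, reported as effect moderation, would read as evidence that more use produces more benefit. The data could not distinguish that from self-selection. The Discussion presents engagement data as a valued product of the trial, so such a result is likely to be noticed.

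**Working it through.** The protocol gives no figure to reproduce. The check is structural, followed by an illustration on stated assumptions.

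**1. Timing, from the Procedure section**

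| Event | SCO-CMC | Waitlist |
|---|---|---|
| Pre-test | before randomisation | before randomisation |
| Programme access | after allocation and contact | after the third measures |
| Outcomes | weeks 4 and 12 | weeks 4 and 12 |
| Programme metrics before the last outcome | yes | none possible |

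Usage metrics recorded later for the waitlist fall after its last planned outcome, so they cannot enter the comparison. The article does not say that the self-reported practice item is put to the waitlist. If it were, the answer would still be given after randomisation and could be affected by allocation.

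**2. Estimability**

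Let G = 1 for SCO-CMC and 0 for waitlist, and let E be engagement. Moderation is b3 in

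Y = b0 + b1·G + b2·E + b3·(G·E).

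Here b2 is the engagement slope in the waitlist, and b3 is the SCO-CMC slope minus that slope.

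- *Waitlist E set to 0.* Then G·E = E for every participant. With 48 per arm the four-column design matrix has rank 3, and the largest difference between the E and G·E columns is 0. Only the sum b2 + b3 is identified.
- *Waitlist E left undefined.* There are no data on b2. Again only the SCO-CMC slope, b2 + b3, can be estimated.

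The missing piece, b2, is the one that would show how far engagement-prone people improve anyway.

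**3. What the within-arm slope can show when nothing is moderated**

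*Analytic illustration.* Assume no programme effect, normally distributed engagement split at its median, and correlation r between engagement and improvement. The mean of the upper half of a standard normal is 0.798, so the high-minus-low gap is 2 × 0.798 × r.

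- r = 0.2: 2 × 0.798 × 0.2 = 0.32 SD of improvement
- r = 0.3: 2 × 0.798 × 0.3 = 0.48 SD of improvement

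These are SDs of change. If the pre-post correlation is 0.7 (an assumption), the SD of change is √(2 × (1 − 0.7)) = 0.77 outcome SD, and the gaps become about 0.25 and 0.37 outcome SD.

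*Simulation.* 20,000 replicates; 40 analysed per arm (the Sample size section's figure before allowance for dropout); a true effect of d = 0.5 for everyone, so no moderation. Motivation correlates a with engagement and b with outcome, so the engagement-outcome correlation is a × b.

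| a | b | a × b | Engagement slopes with p < 0.05 | Apparent d v waitlist: high / low engagers |
|---|---|---|---|---|
| 0 | 0 | 0 | 5.0% | 0.50 / 0.50 |
| 0.3 | 0.3 | 0.09 | 8.5% | 0.57 / 0.43 |
| 0.5 | 0.3 | 0.15 | 15.1% | 0.62 / 0.38 |
| 0.5 | 0.5 | 0.25 | 34.4% | 0.70 / 0.30 |
| 0.7 | 0.5 | 0.35 | 61.9% | 0.78 / 0.22 |

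Motivation alone can therefore look like moderation. How often depends on correlations that the protocol does not give.

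**The case against.** The case on the other side has several parts.

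- *The analysis is only to be explored, in a trial that calls itself exploratory, and feasibility is the first use named.* This stands. It limits the weight of the point, and nothing here enters the group-by-time test or the intention-to-treat analysis.
- *The protocol writes down no group-by-engagement model; a dose-response analysis within SCO-CMC can be fitted, and the model form may be in the analysis plan.* The within-arm analysis can indeed be fitted. But it does not estimate moderation of a between-arm effect, which is what the text promises. No further detail in an analysis plan can supply waitlist engagement under this access schedule.
- *The magnitudes are not trial figures.* This stands. The correlations are assumptions, no median split is planned, and weak confounding (a = b = 0.3) raises false positives only from 5.0% to 8.5%, with a gap of 0.57 − 0.43 = 0.14 SD. The structural point needs none of these numbers.
- *A complier estimate has its own weakness.* This stands. With a module-completion threshold, people below it may still benefit, because the four modules cover different content.

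A reader might also infer that the per-protocol analysis has the same flaw, by setting engaged SCO-CMC users against the whole waitlist. The documents do not support that. The article says "We will perform Intention to Treat and Per Protocol analyses" but does not define the per-protocol population, a detail an article can leave to the fuller document. That criticism is not made here.

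**Conclusion.** The stated analysis cannot deliver what it claims. Observed engagement is post-randomisation and confined to SCO-CMC throughout the compared period, so its moderation of the treatment effect is not estimable. This follows from the access schedule alone.

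The analysis that can be run is a within-arm association open to confounding. With no programme effect and an assumed correlation of 0.2 to 0.3, high and low engagers would differ by about 0.32 to 0.48 SD of improvement; with weaker correlations the gap is proportionally smaller. These are illustrations, not estimates of bias in this trial.

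It would be wrong to infer that the trial's efficacy result is compromised. The intention-to-treat comparison does not use engagement. The point is limited to what may be concluded about engagement, and it is worth correcting before analysis.

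**What to change.** 1. Restrict moderator analyses to variables measured before randomisation, for example age, gender, or baseline K-10 or SCS-SF score.
2. Keep the engagement variables as feasibility data. Report their association with outcome within SCO-CMC only, labelled descriptive and non-causal.
3. If an effect among users is wanted, add as a sensitivity analysis a complier-average causal effect with randomisation as the instrument. Fix a low threshold in advance, for example any programme use, and vary it. The design suits this, because the waitlist has no access code before its last outcome and non-compliance is one-sided.

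Cost: a change of wording, plus one model if step 3 is adopted. No data collection or sample size changes. Step 3 has two downsides to state: a wider interval than a naive comparison of users, and the exclusion assumption that being assigned to SCO-CMC has no effect on those whose use stays below the threshold. If partial users do benefit, the complier estimate is too large, which is the reason for a low threshold. It also answers a different question from dose-response.
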